## Methods

### Study design

The design of this study is a 1:1 single assessor-blinded cumulative adaptive cluster-randomized controlled trial, conforming to the Consolidated Standards of Reporting Trials (CONSORT) statement extension for pragmatic trials [25], with the intervention administered in real-world settings and conditions (trial pragmatism illustrated in Additional File 1). The cumulative adaptive design allows for modification upon evaluation of a subgroup in order to more accurately determine the required sample size, as well as whether changes need to be made to the method before the continuation of the trial [26]. Items from the World Health Organization Trial Registration Data Set are available on the ClinicalTrials.gov registration page (NCT03473821). This protocol adheres to the Standard Protocol Items: Recommendations for Interventional Trials (SPIRIT) guidelines [27], procedures of which are outlined in Fig. 1 (SPIRIT checklist available as Additional File 2). Ethical approval has been granted by the Regional Ethical Review Board in Lund, Sweden (Dnr 2016/413, Dnr 2018/927).

**Fig. 1 Fig1:**
[figure not shown]
Protocol schedule of forms and procedures

### Participants and randomization

Approximately 106 participants are recruited according to inclusion criteria (Table 1) from physical therapy clinics in Sweden. Physical therapists (PTs) fulfilling inclusion criteria (Table 1) from these clinics are included in the trial. The eligibility criteria for both PTs and participants allow for the recruitment of a sample of knee-injured people and their PTs representative of the population. To avoid contamination, participating clinics are block randomized by a third party using a random numbers generator and sealed opaque envelopes to either the experimental or CaU condition.

**Table 1 Tab1:** Participant and physical therapist inclusion and exclusion criteria

Participants	
Inclusion	Exclusion
- Men and women 16 years or older - Traumatic knee injury (e.g., ligament, meniscal, patellar, or chondral injury), with or without surgical intervention, and involving one or more knee structures - Currently undergoing physical therapist-supervised rehabilitation training - Have reached the stage in their rehabilitation which includes single-leg hop training, as well as a change of direction - Active before the injury in recreational or competitive physical activity, with a goal of returning to physical activity	- Any degenerative knee disorder (e.g., osteoarthritis), or other disease or disorder (e.g., spine disorder, neurological disease) overriding the traumatic knee injury - Reached end-stage rehabilitation (i.e., have undergone a return to physical activity evaluation by their physical therapist, or is estimated to return less than 12 weeks from potential inclusion date) - Do not understand the languages of interest (Scandinavian languages, English)
**Physical therapist**	
**Inclusion**	
- At least 2 years’ experience of treatment with training for musculoskeletal disorders	
- Treat patients with a knee injury on a weekly basis	

Clinics, as opposed to participants, are randomized in order to avoid familiarization with both conditions within the same clinic or the individual PT, a potential source of contamination which could influence intervention adherence and therefore skew results. In accordance with the Swedish health care system, participants select their clinic, and clinics do not actively advertise in order to recruit patients (making randomization at the participant level impossible), so self-selection of a treatment arm is theoretically random and blinded. PTs are given information on the methodology of their assigned intervention arm to allow them to recruit participants from their population.

Due to the nature of the design, as well as practical constraints (i.e., necessity of familiarity with intervention, staff availability), neither the study coordinator (SC), participants, nor PTs can be blinded. As a result, the test leader is blinded to the treatment condition and un-blinding is not permissible. Final data analysis is performed by a blinded third party in order to avoid potential bias.

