### Procedure

All knee injuries from the PTs patient pool are reported to the SC during weekly contact, in which the SC reminds PTs of inclusion criteria and actively seeks information on knee-injured participants in order to approach all potential participants in the patient pool. The number of patients approached and invited (i.e., eligible, ineligible, and declined participation) will be recorded. The SC contacts potential participants that have consented to a pre-screening interview, during which information is provided, inclusion, and exclusion criteria are verified, and, if eligible, the participant is invited to take part in the study. Information provided to potential participants includes only that there is a “mental training intervention” with no details which could be used to replicate the intervention, adhering to Swedish ethical guidelines for participant informed consent. Following pre-screening, the SC has regular contact with participants and physical therapists in order to receive updates on patient progression through rehabilitation. This ensures proper inclusion timing and reduces the risk of late inclusion by reducing dependency on physical therapists with regard to inclusion criteria, as well as ensuring that eligible participants are included in the trial. Rehabilitation during this period is provided according to rehabilitation protocols prescribed at the discretion of the PT until the participant is able to complete single-leg hop tasks, ensuring proper inclusion timing. When the hop ability criterion is confirmed by the PT, written information is provided, and baseline testing takes place, during which the test leader collects informed consent (Additional File 3 – Informed Consent Materials). The intervention then begins, implementing either CaU or MOTIFS training in the clinical setting during treatment. The intervention period is 12 weeks, as studies have shown that physical [28] and psychological [29] factors can be improved in this time span. MOTIFS training accounts for approximately 20 min [30] in a typical 60-min training session. At least 3 supervised or at-home training sessions are performed per week, whereof at least 6 are supervised by a participating PT during the intervention period, resulting in an intervention dose of 36 possible training sessions, with intensity prescribed by the PT. Participants and PTs are made aware of the possibility to end their involvement in the study. Participants may remove themselves at their discretion, or worsening symptoms may require the PT to change treatment strategy. To ensure that participants complete self-report questionnaires, telephone contact may be initiated.

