### Statistical analyses

#### Sample size

Based on previous studies examining ACL-RSI [49] and side-hop function [50], a preliminary sample size was estimated, to be used in the first phase of this adaptive RCT, which resulted in *n*=106 participants. This included adjustments for potential cluster effects using a preliminary Intra-Cluster Correlation Coefficient (ICC). An approximation is required as comparable studies are unavailable to reliably perform a sample size estimation. This is necessary in this phase in order to evaluate whether an intervention effect is detectable and within practical limitations, which will thereafter inform more accurate sample-size estimations.

A new sample size will be calculated by a blinded third-party member of the data management committee using collected data from an interim analysis, therefore allowing for more accurate between-group differences in the main outcomes. Observed within- and between-cluster variance will also be calculated in order to more accurately estimate an Intra-Cluster Correlation Coefficient (ICC, denoted as *ρ*). This will be performed using the formula $$ \rho =\frac{s_b^2}{s_b^2+{s}_w^2} $$ [51] in order to adjust for the fact that different clinics are included in the trial (i.e., potential clustering effects). The adjusted sample size will therefore be calculated using the formula $$ \frac{n_ik\left(1-\rho \right)}{k-{n}_i\rho } $$ [52], along with an estimated 20% drop-out rate, in order to reach a power of 0.80, with significance set at *p*<0.025. As an estimated sample size has been calculated, the new sample size will only be adjusted up; that is, the number of participants included will not be less than *n*=106 required in the original sample-size estimation.

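### The cluster formula for the sample-size re-calculation assumes equal clinic sizes, which the described recruitment does not provide; its n falls short of 0.80 power by an amount that depends on unstated inputs

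*Protocol article*

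**What the plan says.** Under Statistical analyses, Sample size, the article gives a preliminary figure "which resulted in *n*=106 participants", described as already adjusted for clustering with a preliminary ICC. After the interim analysis a blinded third party estimates the ICC (ρ) from the within- and between-clinic variance. "The adjusted sample size will therefore be calculated using the formula" n_i·k·(1−ρ)/(k − n_i·ρ), "along with an estimated 20% drop-out rate, in order to reach a power of 0.80", with "significance set at *p*<0.025". The new size may only go up from 106.

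Under Participants and randomization (text after Table 1), clinics are the unit of randomization, and "participants select their clinic, and clinics do not actively advertise in order to recruit patients". Under Procedure, the study coordinator is in weekly contact with the physical therapists "in order to approach all potential participants in the patient pool".

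The article gives no number of clinics, no value of ρ, no quota or cap per clinic, and no term for variation in clinic size.

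**The concern.** The re-calculation updates ρ and the between-group differences, but it uses a formula in which all clinics are the same size. When patients choose the clinic and everyone eligible is approached, sizes follow case-load and chance. Unequal sizes raise the design effect above the value built into the formula. The error runs one way, towards too few participants, and applies to both main outcomes. At stake is whether the re-calculated n carries the power stated for it.

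**Working it through.** **Inputs.** From the article: power 0.80, significance 0.025 (sidedness not stated, two-sided assumed), 20% drop-out, 106 in total, 1:1. This gives 53 enrolled and 53×0.8 = 42.4 analysed per arm. Assumed, because the article gives none: n_i and k are per arm, k = 5 to 12, ρ = 0.01 to 0.10, cv as below. Normal approximation with z = 2.241 and 0.842, and no small-k degrees-of-freedom correction.

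**Can 106 be reproduced?** No. The effect, SD, ρ and k are not given. A search over standardised effects 0.30 to 1.00, ρ 0 to 0.10 and k 2 to 15 finds combinations that give about 106, all with effects between 0.65 and 0.95. So 106 is attainable but cannot be traced. Below it serves only as an example of an n that the formula could return.

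**What the formula assumes.** With a common clinic size N/k, N = n_i·[1+(N/k−1)·ρ]. Solving for N gives n_i·k·(1−ρ)/(k − n_i·ρ), which is the article's formula. Check with n_i=30, k=6, ρ=0.05: 38.0 by both routes.

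**Unequal clinics.** The design effect becomes 1+[(1+cv²)·m−1]·ρ, with m = N/k. The matching sample size per arm is n_i·k·(1−ρ)/(k − n_i·ρ·(1+cv²)).

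**How uneven by chance alone?** Equally popular clinics give cv ≈ √((k−1)/N). With N = 42.4 this is 0.31 for k=5, 0.41 for k=8 and 0.51 for k=12. Differences in case-load would add to it.

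**One case in full (k=8, ρ=0.05, cv=0.5).**
- m = 42.4/8 = 5.3
- Design effect, equal clinics: 1+4.3×0.05 = 1.215, so n_i = 42.4/1.215 = 34.9
- Design effect, cv 0.5: 1+(1.25×5.3−1)×0.05 = 1.281
- Power: Φ(3.083×√(1.215/1.281) − 2.241) = Φ(0.76) = 0.777
- n per arm restoring 0.80: 34.9×8×0.95/(8−34.9×0.05×1.25) = 45.6 analysed, so 2×45.6/0.8 ≈ 114 enrolled in total, against 106

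**Range.** Each cell gives power at 106, then the total enrolment that restores 0.80 with k held fixed.

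| k per arm | ρ | cv 0.4 | cv 0.5 | cv 0.65 |
|---|---|---|---|---|
| 12 | 0.01 | 0.798; 107 | 0.796; 107 | 0.794; 108 |
| 10 | 0.02 | 0.795; 108 | 0.791; 109 | 0.786; 111 |
| 8 | 0.05 | 0.785; 111 | 0.777; 114 | 0.761; 121 |
| 5 | 0.05 | 0.779; 115 | 0.767; 120 | 0.745; 131 |
| 5 | 0.10 | 0.767; 125 | 0.749; 139 | 0.715; 177 |

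The first and last rows are the extremes for k 5 to 12 and ρ 0.01 to 0.10.

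**Does weighting remove the loss?** No. With optimal weights a clinic of size m contributes information proportional to m/(1+(m−1)ρ). This is concave in m, so for fixed N and k equal sizes are best. Optimal weights recover only part of the loss.

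**The case against.** **The planned test is not adjusted for clustering.** Data analysis names independent-samples t tests and leaves clustering to sensitivity analyses. An unadjusted test rejects more than 80% of the time at the same effect: in the worked case, Φ((3.083×√1.215−2.241)/√1.281) ≈ 0.85. This is correct, but the rejections are bought with false positives. The actual level is 2[1−Φ(2.241/√1.281)] ≈ 0.048. By the same formula it runs from 0.027 (design effect 1.031: k=12, ρ=0.01, cv 0.4) to 0.12 (design effect 2.106: k=5, ρ=0.10, cv 0.65). Power stated at 0.025 is not rescued by a test that does not hold 0.025.

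**The size rests on assumed k, ρ and cv.** This stands. A reader might infer that the trial misses 0.80 by a wide margin. The documents do not support that. Chance alone supports a cv of only about 0.3 to 0.5, and a cv of 0.8 or 1.0 has no basis in the text. With low ρ and many clinics the loss is under one point.

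**106 is preliminary and can only rise.** This also stands. If 106 exceeds the corrected need, 0.80 may still be reached, so a flat statement that 0.80 is not delivered would go too far. But any upward revision uses the same formula and has the same bias.

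**Feasibility.** A reader might infer that the error would tip the article's example of an unrealistic size, more than 100 per group. In the table it does not: the largest total, 177, is about 89 per group. It could matter only if the formula's own n were already close to that limit.

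**Silence on quotas.** A condensed article may omit a recruitment cap held in a fuller document. The point therefore rests on the recruitment as described and the formula as written.

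**Conclusion.** The point holds in a limited form. The formula is exact only for equal clinics, and the recruitment described gives no reason to expect them. For any test valid at 0.025 under clustering, the direction is then certain whenever ρ>0: the formula's n has less than the stated 0.80. The size is not established. Under the assumptions above, power is about 0.75 to 0.80 at cv 0.4 to 0.5 and about 0.71 to 0.79 at cv 0.65. The larger losses need few clinics together with ρ of 0.05 or more. The correction is worth making because the rule is stated explicitly and the missing term is easy to add. It does not show that 106 is inadequate.

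**What to change.** In Sample size, replace the formula by n_i·k·(1−ρ)/(k − n_i·ρ·(1+cv²)), and state the k, ρ and cv used.

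Take cv as the value expected at full enrolment, not the raw interim value, which is too large because clinics are still small. With 8 equally popular clinics, chance alone gives √(7/25) = 0.53 at 25 per arm, against √(7/42.4) = 0.41 at 42.4. One projection is cv_final² = cv_interim² − 1/m_interim + 1/m_final, with m the mean clinic size. For example, with k=8 and an interim cv of 0.60: 0.36 − 0.32 + 0.189 = 0.229, so cv_final ≈ 0.48. Because m_final depends on the new n, repeat the step once or twice.

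If the resulting n is not feasible, keep the planned n and restate its power on this basis.

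The cost is small: one extra term from clinic counts that the trial already holds, with no treatment comparison needed for it. The downside is a slightly less favourable power or n. If the power is restated, no extra patients are needed.

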#### Data analysis

The analysis will be done using the IBM SPSS statistical software package (IBM Corp., Armonk, New York, USA). Primary analyses of the entire sample will be done according to intention-to-treat principles. A dose-response analysis will be performed to determine effective adherence. Per-protocol analyses will be performed for those participants with at least 70% adherence (corresponding to two trainings per week), as a preliminary estimate of the effective number of training occasions. This is in order to eliminate cross-over and drop-out effects in the total sample, as well as to evaluate the training for those that have reached a pre-defined level of adherence deemed acceptable to have an effect. Sensitivity analyses will be performed to determine whether within-cluster correlations indicate potential effects due to being clustered, for example, by the clinic or by PT. Patient cross-over (i.e., patients changing clinics) is a low-risk possibility and will be recorded in case of occurrence. All outcome variables will be examined for normality using appropriate testing (e.g., Kolmogorov-Smirnov). Complete-case analyses are the primary analyses, and sensitivity analyses will be done depending on the number of missing values. Missing values are not expected to be extensive, and if less than 5% of data is missing, the whole data set will be analyzed along with a sensitivity analysis with appropriate imputed values. If between 5 and 40% of data is missing, appropriate multiple imputation methods will be used, which will be informed by blindly assessing results of the interim analysis, and a complete-case analysis will be done with appropriate sensitivity analyses. If over 40% is missing, a complete case analysis will be done with no sensitivity analysis.

Results will be analyzed using independent samples *t* tests to examine between-group differences of the change from baseline to a 12-week follow-up. Where appropriate, equivalent non-parametric Wilcoxon signed-rank testing will be used to compare between-group differences. The main analysis will focus on the two main outcomes, with secondary outcomes acting as support for these. Secondary outcomes therefore carry less weight and issues with potential error due to the number of evaluations will be discussed when results are presented.

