Limitations include that only the test leader is blinded to condition assignment due to the nature of the design. As the study coordinator is not blinded, bias cannot be ruled out during recruitment. Information to participants includes a brief description of the aims of the study in line with Swedish ethical guidelines, which may influence participants’ decision to participate or their behavior during the trial (i.e., if aware of a mental training intervention, more focus may be placed on mental aspects). However, as the participants receive no specific information, and imagery is assessed as a compliance measure, this is not seen as problematic. A further limitation includes that previous studies do not provide relevant data for sample size calculation. Mean differences, standard deviations, and variance are therefore theoretical, leading the authors to use an adaptive design in order to collect data which may be used for sample-size re-calculation. Simulation analyses, which may provide more accurate estimations, were not used to estimate sample size as these theoretical and estimated values would not provide reliable results. This highlights the adaptive nature of this trial and having collected data will provide information necessary to perform reliable sample size and power calculations for future research. This trial presents challenges in that it introduces the more holistic MOTIFS model, which shifts the clinical paradigm and places more focus on the individual and their context-specific needs from a psychological perspective. In order to aid in this, individual visits with the SC, as well as guidance and workshops, will smooth the transition to the novel MOTIFS training model.

Along with publication in a peer-reviewed journal, results of the study will be communicated via a popular science article in order to inform potential end-users of the outcome of this trial, with the aim of making the MOTIFS model readily available for use by end-users.

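### The statement that arm self-selection is random and blinded can cover only the choice of clinic; arm-aware staff recruit after allocation, and the planned unadjusted change comparison can be biased by a transient baseline imbalance

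*Protocol article*

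**What the plan says.** All references are to the protocol article.

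- **Allocation** (Participants and randomization): "participating clinics are block randomized by a third party using a random numbers generator and sealed opaque envelopes". The unit is the clinic.
- **Route to an arm** (same section, text after Table 1): patients pick their own clinic and clinics do not advertise, "so self-selection of a treatment arm is theoretically random and blinded".
- **Who recruits** (same text): "PTs are given information on the methodology of their assigned intervention arm to allow them to recruit participants from their population". The next paragraph adds that "neither the study coordinator (SC), participants, nor PTs can be blinded"; the test leader is blinded.
- **Steps to entry** (Procedure): therapists report knee injuries weekly to the coordinator. "The SC contacts potential participants that have consented to a pre-screening interview", checks the criteria and invites. "When the hop ability criterion is confirmed by the PT", written information is given and baseline testing follows, where the test leader takes consent.
- **Safeguards** (Procedure): the coordinator tries to reach every potential participant, and counts of eligible, ineligible and declining patients are recorded.
- **Admitted limitation** (Discussion): "As the study coordinator is not blinded, bias cannot be ruled out during recruitment". Therapists are not mentioned there as a source of bias.
- **Main analysis** (Data analysis): independent samples t tests "to examine between-group differences of the change from baseline to a 12-week follow-up". No covariate is named.

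**The concern.** In a cluster-randomised trial, randomising clinics protects the comparison of clinics. It protects the comparison of participants only if recruitment within clinics is unaffected by knowledge of the arm. Here the people who report patients, check criteria, invite them and decide when they are ready all know the arm. Two entry conditions in Table 1 also call for judgement: having reached the hop-training stage, and not being expected to return to activity within 12 weeks. A reader who takes the quoted statement at face value would conclude that the arms are comparable by design at participant level, which the described procedure does not secure.

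If the arms then differ at baseline on ACL-RSI or side hop, the planned analysis matters. A change score subtracts the baseline in full. When the baseline difference is partly transient, that over-corrects and leaves a difference in change with no treatment effect. The interim rule and the sample-size recalculation also use between-group differences in the main outcomes, so such a bias would reach those decisions too.

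**Working it through.** **1. Order of events.** No randomisation date is given. Trial status puts clinic enrolment from October 2017 and participant enrolment from March 2018, and therapists are briefed on their arm so that they can recruit. Allocation before recruitment is therefore an inference, but a firm one.

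**2. Which steps the statement can cover.**

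| Step | Done by | Aware of arm? |
|---|---|---|
| Choice of clinic | Patient | May well be unaware |
| Reporting of the injury | Therapist | Yes |
| Pre-screening, criteria, invitation | Coordinator | Yes |
| Confirmation of hop criterion, hence timing of entry | Therapist | Yes |
| Consent and baseline tests | Test leader | No |

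Only the first row fits the statement. The Discussion's limitation covers the third row but not the second and fourth.

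**3. Bias of the change comparison.** The article gives no imbalance, correlation or SD, so these are assumptions: baseline imbalance b = 0.2 to 0.5 SD, baseline to 12-week correlation r = 0.3 to 0.7, equal SDs at both times, and SD 20 for ACL-RSI. The slope of change on baseline is r − 1, so with no true effect the difference in change is −(1 − r) × b.

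- Smallest: (1 − 0.7) × 0.2 = 0.06 SD; 0.06 × 20 = 1.2 points.
- Largest: (1 − 0.3) × 0.5 = 0.35 SD; 0.35 × 20 = 7 points.

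The arm that starts lower appears to gain more, so the direction depends on which arm that is. The documents give no basis for saying which. For scale only, the interim continuation criterion for ACL-RSI is 5 points.

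**4. False-positive rate.** 106 participants at 1:1 give 53 per arm; with 20% drop-out, 53 × 0.8 = 42.4. A simulation with a true effect of zero used 42 per arm, two-sided 0.025 (the article states p<0.025 without sidedness), 20,000 runs and no clustering. Ranges are over the assumed b and r.

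| Nature of the imbalance | t test on change | Baseline-adjusted |
|---|---|---|
| Measured baseline, regresses to the mean | 0.033 to 0.184 | 0.022 to 0.026 |
| Fully stable baseline difference | 0.023 to 0.026 | 0.034 to 0.261 |
| Unmeasured prognosis | 0.07 to 0.75 | 0.10 to 0.82 |

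Neither analysis is safe in every row.

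**5. Precision.** With equal SDs, the change score has variance 2σ²(1 − r) and the baseline-adjusted score σ²(1 − r²). The ratio is (1 + r)/2, which is 0.65 at r = 0.3 and 0.85 at r = 0.7. The adjusted comparison therefore has about 35% to 15% less variance, whether or not there is selection.

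**6. The plan's own figure.** The article gives no figure on this point to reproduce. The nearby n=106 is not disputed here, and cannot be rebuilt because its effect size, SD, ICC and cluster size are not stated.

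**The case against.** The statement is about how patients reach a clinic, and it says only that this is theoretically unrelated to arm. A reader might infer that the trial uses clinic choice as its allocation method, or is not truly randomised. The article does not support that: clinics are randomised by a third party with concealed envelopes, and this balances clinic case-mix in expectation. This part of the objection stands.

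A reader might also infer that staff hand-pick participants. That is not supported either. The aim is to approach everyone, refusals are logged, and coordinator contact is meant to reduce dependence on therapists' judgement. This stands as well, but these measures make selection visible without preventing it, and the coordinator is unblinded too.

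Next, the regression-to-the-mean bias is conditional, and its inputs are assumed. If the baseline difference is fully stable, the planned test is valid and baseline adjustment does worse. If selection acts on unmeasured prognosis, neither analysis protects. This stands and limits what may be claimed: the documents do not show that the planned test will produce a false effect.

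The coordinator's part is already disclosed, and a fuller analysis plan might name covariates. But the disclosure leaves out the therapists and does not correct the statement, and the article itself names the main test and states it without adjustment.

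**Conclusion.** The concern holds in a limited form. The claim that arm self-selection is random and blinded is true at most of the choice of clinic. For the later recruitment steps it is contradicted by the article's own account of who recruits, and the stated limitation covers only one of the two unblinded parties.

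The planned change comparison is open to a bias of 0.06 to 0.35 SD (1.2 to 7 ACL-RSI points at SD 20), in either direction, if a baseline imbalance of 0.2 to 0.5 SD is transient and r lies between 0.3 and 0.7. It is nil if the imbalance is fully stable. None of these inputs comes from the article, and the calculation ignores clustering. The case for adjustment does not rest on selection alone: adjustment also deals with transient or chance imbalance and cuts variance by about 15% to 35% over the same range of r. It does not cure selective recruitment on factors that are not measured.

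**What to change.** 1. **Wording.** In Participants and randomization, replace the claim with a plain statement that clinics are randomised and that participants are identified and recruited after allocation by staff who know the arm. In the Discussion, extend the recruitment-bias limitation from the coordinator to the therapists.
2. **Analysis.** Make the main comparison for each main outcome a model of the 12-week score adjusted for its baseline score, optionally with injury history and treatment type, which are already collected. Keep the unadjusted change comparison as a prespecified sensitivity analysis, since adjustment can do worse when baseline differences are fully stable. If the two disagree, report both and discuss why.
3. **Reporting.** Present the existing log of approached, eligible, ineligible and declining patients, and the baseline characteristics, by arm and by clinic.

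Eligibility sign-off by the blinded test leader is not recommended. It would come after most of the selection, would rely on information from unblinded staff, and could put that person's blinding at risk.

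The cost is slightly more analysis work and a less favourable description of recruitment. No new data are needed. Trial status reports 35 participants included, fewer than the 50 implied by 25 in each group, so at the time of writing the change could still have been fixed before the interim analysis.
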